### Withdrawal

Reasons for withdrawal were if patient were included in error (did not fulfil inclusion criteria or did fulfil one or more exclusion criteria as well if patients were enrolled in the study at a previous ICU-stay) or if patient or relatives did not consent to participation in the study.

### Baseline Patient Characteristics

The characteristics collected at baseline include:

- Patient demographics (age and gender)
- Chronic comorbidities (a history of heart failure, hypertension, diabetes, stroke, prior MI etc.)
- Primary reason for ICU-admission (as per SAPS 3 categories)
- Category of ICU-admission (medical, surgical, acute, elective)
- Timeline parameters (time of inclusion, time of ICU-admission, time of hospital admission etc.)
- Infection status at admission
- ICU-admission source (operating theatre, ward, emergency department etc.)
- Physiology at baseline (PAF-ratio, blood pressure, pulse etc.)
- Therapy at baseline (noradrenaline, insulin etc.)
- Respiratory therapy at baseline

# Analysis

### Outcome Definitions

The primary outcome is time in days to liberation from mechanical ventilation. Liberation from mechanical ventilation is defined to occur on the second of two consecutive ICU-days without the need for either IV or NIV. Liberation from mechanical ventilation was also considered to occur on the day of ICU discharge if cessation of mechanical ventilation occurs on the same day as ICU-discharge in patients that are not readmitted to the ICU within two days. The competing risk of death is said to occur if patients died before or within 24 hours from liberation from mechanical ventilation. Patients are censored if they were moved to a different hospital while still receiving mechanical ventilation or at 30 days if still receiving mechanical ventilation.

Secondary outcomes are the risk of death from any cause at 30 days, PaO2/FiO2-ratio (PAF-ratio) on the first day of ICU-admission and last measured PAF-ratio in patients dying within 5 days from inclusion.

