### Outcome Assessment

Patients were followed for 30 days after inclusion for collection of clinical data from their ICU-stay including timing of liberation from mechanical ventilation and were subsequently followed for a year for the occurrence of death from any cause.

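### The liberation rule dates the same end of ventilation up to two days apart depending on ICU discharge, and gives survivors discharged the next day no outcome status

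*SAP*

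**What the plan says.** All the rules are in the SAP, Analysis, Outcome Definitions. The time scale is whole days: "The primary outcome is time in days to liberation from mechanical ventilation".

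- **General liberation rule:** "Liberation from mechanical ventilation is defined to occur on the second of two consecutive ICU-days without the need for either IV or NIV".
- **Discharge exception:** liberation also falls "on the day of ICU discharge if cessation of mechanical ventilation occurs on the same day as ICU-discharge in patients that are not readmitted"; the window for such a return is two days.
- **Competing event:** "The competing risk of death is said to occur if patients died before or within 24 hours from liberation from mechanical ventilation".
- **Censoring:** there are two routes, and both need the patient to be ventilated: "moved to a different hospital while still receiving mechanical ventilation or at 30 days if still receiving mechanical ventilation".

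Under Outcome Assessment, "Patients were followed for 30 days after inclusion for collection of clinical data from their ICU-stay". The SAP does not say whether an ICU-day is a calendar day or a 24-hour block. It has no rule for a patient who leaves the ICU after exactly one ventilation-free ICU-day, and nothing lets ward days count towards the two days required.

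**The concern.** The primary analysis is a cause-specific Cox model, which needs one time and one status for each patient. The general rule dates liberation at the end of a confirmation period; the exception dates it at cessation. Two patients who come off ventilation on the same day can then have different event times only because one left the ICU sooner.

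This matters if discharge timing is related to the markers. The SAP's Background says that sTM and Syndecan-1 rise with more severe disease, and sicker patients may be kept longer. If so, the timing error would differ by marker level and could produce an association with liberation where none exists. For next-day discharges the analyst would have to choose a status that the plan does not give, possibly after seeing the data.

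**Working it through.** The SAP gives no sample size, event count or discharge data, so there is no planned figure to reproduce. The check applies the written rules case by case.

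**Classification.** Let d be the last day with any IV or NIV, here day 5, with no later ventilation and no readmission.

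| ICU discharge | Day 5 not a free day (natural reading) | Day 5 counted as free |
|---|---|---|
| Day 5 (d) | liberated, day 5 | liberated, day 5 |
| Day 6 (d+1), alive to day 30 | no status | liberated, day 6 |
| Day 6 (d+1), dies day 20 | competing death, day 20 | liberated, day 6 |
| Day 7 or later | liberated, day 7 | liberated, day 6 |

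On the natural reading the offset is 7 − 5 = 2 days; on the other it is 6 − 5 = 1 day.

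The day-6 discharge on the natural reading, rule by rule:
- General rule: only day 6 is a free ICU-day, and two are needed. Not met.
- Exception: cessation is day 5 and discharge day 6. Not met.
- Censoring: not ventilated at a transfer or at day 30. Not met.
- Competing death: not met by a survivor. A death on day 20 precedes a liberation that was never recorded, so it is met literally, 20 − 5 = 15 days after the last ventilated day.

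Two smaller gaps appear on the natural reading. A patient who stops on day 29 and stays in the ICU has a second free day at 31, past follow-up, yet is not ventilated at day 30. A same-day discharge readmitted within two days, with neither further ventilation nor two free ICU-days, also has no status.

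**Death window.** Take a death 30 hours after stopping.
- Patient still in the ICU: liberation would be dated d+2, so the death comes before it or within 24 hours of it. Competing event.
- Same-day discharge: liberation is at d and 30 > 24. Liberation. (If the window runs from the hour of discharge, this holds when discharge came within 30 − 24 = 6 hours of stopping.)

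On whole days the contrast does not depend on the hour. Any death on d+2 is more than 24 hours after every moment of day d, so it follows a liberation after same-day discharge; in the ICU patient it is a competing event.

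**Illustrative size of the dating offset.** Every input is assumed: two marker groups with the same exponential time to stopping (median 3, 5 or 7 days, rounded up to whole days), event time d for same-day discharge and d+2 otherwise, end of follow-up at day 30, n = 20,000 per run, Efron ties, no covariates. The true hazard ratio (high versus low marker) is 1.

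| Same-day share, low / high marker | Median 3 | Median 5 | Median 7 |
|---|---|---|---|
| 20% / 20% | 1.000 | 0.982 | 1.005 |
| 30% / 10% | 0.917 | 0.956 | 0.979 |
| 40% / 20% | 0.923 | 0.940 | 0.976 |

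The standard error of the log hazard ratio is about 2/√20,000 = 0.014, so single runs wander by 0.02 or so, as the first row shows, and the median-7 results are hard to tell from noise. A separate run with a daily death hazard of 0.03 and shares of 40–60% versus 20% gave 0.83 to 0.96, against 0.97 to 1.01 when everyone was dated at cessation.

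**Unclassified group.** With assumed shares of 20–30% (low marker) versus 10–15% (high) and again no true effect, the hazard ratio depends on the coding chosen:
- kept at risk and unliberated to day 30: 1.21 to 1.46
- censored at discharge: 1.06 to 1.24
- dropped: 0.95 to 1.01
- liberated on the discharge day: 0.96 to 1.00

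The SAP states none of these codings.

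**The case against.** The best defence is that ICU-day is undefined. If the day ventilation stops may count as the first free day, the offset shrinks to one day and next-day discharges are liberated. This stands as a qualification. But a day on which a patient was ventilated is not naturally a day without need of ventilation, the one-day offset would remain, and a primary outcome should not turn on an undefined term.

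Other limits also stand:

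- A reader might infer that every next-day discharge lacks a status. That is exact only for those alive through follow-up; a later death is literally a competing event, so it is misclassified and not unclassified.
- A reader might take hazard ratios well above 1 as the bias this plan will produce. They come from keeping next-day discharges at risk to day 30, which the SAP does not prescribe: its day-30 censoring is only for patients still ventilated. Other codings bring the value to about 1.
- A reader might assume that next-day discharge is common, or that patients discharged early have low markers. The SAP gives no discharge timing, and its Background also reports that sTM and Syndecan-1 correlate poorly with hypoxaemia and need for ventilation.
- The simulated ratios are unadjusted. The planned covariates (PAF-ratio, septic shock, kidney injury, bilirubin and others) may absorb part of any link between severity and discharge.

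The study is declared exploratory. That excuses the absence of a power calculation and of multiplicity control, but not a primary outcome that cannot be derived for some patients.

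**Conclusion.** The point holds in a limited form. The written rules make the primary event time depend on ICU discharge as well as on ventilation: by two days on the natural reading, by one day if the cessation day counts as free. On the natural reading they also leave survivors discharged on d+1 without a status, turn later deaths in that group into competing events, and apply the death window from unequal starting points.

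The number of patients affected is unknown. An unadjusted hazard ratio of about 0.92 to 0.98 for a 20-point difference in same-day discharge, lower for larger differences, shows direction and rough size under assumed inputs. With equal shares the distortion disappears. The documents do not support a stronger conclusion, that the analysis is biased by a known amount or in a known direction overall: the offset pulls the ratio below 1, while the unclassified group can push it above 1 or leave it near 1 depending on coding. The defect is in the rule itself and should be settled before analysis.

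**What to change.** Amend Outcome Definitions as follows:

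1. Define an ICU-day as a calendar day, and state that a day with any IV or NIV is not ventilation-free.
2. Date liberation for every patient from one anchor, the last day with IV or NIV.
3. Confirm it by two days alive without ventilation in the ICU or, after discharge, by no ICU readmission within two days, the criterion the SAP already uses.
4. Classify patients discharged after one free ICU-day, and same-day discharges who are readmitted, under this rule. State the status of a stop too close to day 30 to be confirmed.
5. Count death within one common window from that anchor as the competing event. Two days would match the confirmation period.

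A patient stopping on day 5 then has event time 5 whether discharged on day 5, 6, 7 or later.

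The cost is a change of wording and a re-derivation from ventilation, discharge, readmission and death dates that the present rules already need. Because clinical data are described as coming from the ICU stay, ventilation on the ward after discharge may not be captured; say so as a limitation. Reporting how many patients fall into each discharge pattern would show how much the change matters.

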### Objectives

The broader aim of the study is to expand the knowledge on the connection between endothelial dysfunction and patient-important outcomes in the setting of critically ill patients with acute respiratory failure. If a connection between the duration of mechanical ventilation and endothelial dysfunction is found it could lead to better prognostication and identification of the sickest patients at ICU-admission. This could pave the way for clinical trials testing a targeted treatment against the endotheliopathy to shorten the time that mechanical ventilation is required.

The objective of the study is to estimate the impact of endothelial dysfunction as measured with sTM, Syndecan-1 and PECAM-1 on the time to liberation from mechanical ventilation in a general ICU population admitted with acute respiratory failure.

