### Analysis Methods

The effect of sTM, Syndecan-1 and PECAM-1 on the primary outcome is analysed using cox regression and reported as cause-specific hazards using the method of Ozenne et al.^21^ A separate model is fitted for each of the explanatory variables of interest and each model is controlled for the abovementioned variables.

The effect of the markers of endothelial damage on the risk of death from any cause at 30 days is modelled with cox regression and controlled for the same variables as the analysis of the primary outcome.

We model the effects of continuous variables with restricted cubic splines with 2 knots^22^ if the introduction of splines significantly improves model fit as evaluated by the Wald Statistic.

The effect of the markers of endothelial damage on the PAF-ratio on the first day of ICU-admission and on last PAF-ratio in patients dying within 5 days of inclusion is modelled with linear regression and controlled for COPD, age, respiratory infection and shock (defined as need for vasopressor and a lactate >= 2).

All models will be examined for standard measures of model fit and assumptions and the included variables will be transformed as appropriately. We test for biological plausible interactions such as between levels of the biomarkers of endothelial damage and septic shock or respiratory infection. Interaction terms will be kept in the model if they are significant in the multivariable analysis based on the p-value for the effect of the interaction term.

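### The primary outcome dates the same end of ventilation two days later for patients who stay in the ICU than for patients discharged that day

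*SAP*

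**What the plan says.** Under Outcome Definitions, "The primary outcome is time in days to liberation from mechanical ventilation". Two routes lead to the event:

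- **Staying in the ICU.** Liberation is "defined to occur on the second of two consecutive ICU-days without the need for either IV or NIV".
- **Leaving the ICU.** "Liberation from mechanical ventilation was also considered to occur on the day of ICU discharge", and this applies "if cessation of mechanical ventilation occurs on the same day as ICU-discharge in patients that are not readmitted to the ICU within two days".

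Death is tied to the resulting date: "The competing risk of death is said to occur if patients died before or within 24 hours from liberation from mechanical ventilation". Patients are censored on transfer to another hospital while ventilated, "or at 30 days if still receiving mechanical ventilation".

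Under Analysis Methods the outcome is "analysed using cox regression and reported as cause-specific hazards", with one model per marker and a fixed covariate list. The Objectives name time to liberation as the target and look ahead to treatments that might "shorten the time that mechanical ventilation is required". The SAP does not back-date the first route, does not mention the offset, and plans no sensitivity analysis with a common date.

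**The concern.** Two ventilation-free days are a sensible check that liberation has lasted. The first route adds these two days to the event time. The second route uses the same two days only as a readmission check and adds nothing. The recorded time therefore depends partly on where the patient was after ventilation ended.

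A lag shared by all patients would not create an association with a marker. This lag is not shared, because it depends on same-day discharge. Background and Rationale says that sTM and Syndecan-1 rise with severity and predict liver and renal failure. Patients with high values may therefore leave the ICU less often on the day ventilation stops. If so, a marker unrelated to ventilation time would appear to slow liberation, which is the direction the study is looking for.

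**Working it through.** **Dating.** Let D be the last day with any ventilation. D cannot be one of the two ventilation-free days, so the first route gives D+2 at the earliest. The second route gives D.

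| Last ventilated day D | Stays in ICU (D+2) | Discharged on D | Gap |
|---|---|---|---|
| 1 | 3 | 1 | 2 |
| 3 | 5 | 3 | 2 |
| 7 | 9 | 7 | 2 |

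Eligibility requires ventilation on the first ICU day, so D is at least 1 and the first route cannot give an event before ICU day 1 + 2 = 3. Any earlier event must come from the discharge route.

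**Cap.** Take D = 5 and vary the ICU stay after D. A stay of 0 days is dated 5. Stays of 2, 3, 5 and 10 days are all dated 7. A patient discharged on D+1, after one ventilation-free ICU-day, meets neither route and has no defined date.

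**Death window.** The window follows the liberation date. A death on D+2 is a competing event for a patient who stayed in the ICU, but can fall after liberation for a patient discharged on D.

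**Effect on the mean.** If the marker does not affect D, the difference in mean time between low- and high-marker patients is 2 × (same-day share in low − same-day share in high):

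- 10% vs 5%: 2 × 0.05 = 0.1 day
- 20% vs 10%: 2 × 0.10 = 0.2 day
- 30% vs 10%: 2 × 0.20 = 0.4 day
- 40% vs 10%: 2 × 0.30 = 0.6 day

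**Effect on the hazard ratio.** The SAP states no sample size, event count or discharge share, so there is no figure of its own to reproduce. The following was simulated, with these assumptions:

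- a binary marker with no effect on ventilation duration
- geometric ventilation time with mean 3, 5 or 8 days
- daily death hazard 0.04 as the competing event
- D+2 for everyone not discharged on D
- no covariates, and a cause-specific Cox model with Efron ties

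From the SAP comes only the 30-day censoring. There was one run of 20,000 patients per scenario, with a standard error of the log hazard ratio of about 0.016.

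| Same-day share, low vs high marker | HR, mean 3 d | mean 5 d | mean 8 d |
|---|---|---|---|
| 20% vs 20% | 0.969 | 1.005 | 1.020 |
| 10% vs 5% | 0.971 | 0.965 | 0.962 |
| 20% vs 10% | 0.930 | 0.921 | 0.967 |
| 30% vs 10% | 0.855 | 0.918 | 0.930 |
| 40% vs 10% | 0.828 | 0.908 | 0.894 |

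A separate unadjusted rerun gave about 0.98-1.00, 0.92-0.96 and 0.82-0.90 for 10% vs 5%, 20% vs 10% and 40% vs 10%. With both routes dated to D, the hazard ratio was 0.97-1.02 in every scenario, which is 1 within simulation error.

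**False rejection at a nominal 5%** (two-sided, mean 5 days, 1,000 runs):

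| Same-day share | n = 200 | n = 500 |
|---|---|---|
| 20% vs 20% | 5.3% | 4.8% |
| 20% vs 10% | 6.2% | 5.6% |
| 30% vs 10% | 10.2% | 16.4% |
| 40% vs 10% | 13.5% | 29.9% |

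The simulation error here is √(0.05 × 0.95 / 1000) ≈ 0.7 percentage points, so the 20% vs 10% row cannot be told apart from 5%.

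**With adjustment.** In another simulation a null marker was related to same-day discharge only through shock and AKI (odds ratio 0.25 each, overall same-day share 27-42%). The unadjusted HR per SD was 0.93-0.97. Adjusted for those two covariates it was 0.985-0.996. A remaining direct odds ratio of 0.85 per SD for same-day discharge gave adjusted values of 0.96-0.99.

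**The case against.** **The covariates may deal with it.** The Variables section adjusts for septic shock, acute kidney injury and bilirubin, among others, and these are the likely reasons for staying in the ICU. This stands in large part: adjustment removed most of the bias when it ran only through measured covariates. But those covariates describe admission or the first day, while discharge is decided when ventilation stops, so some bias can remain. Statistical Principles also provides for univariable results where relevant, and these have no such protection.

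**A sustained ventilation-free period is a legitimate event.** This is true, and a reader who infers that reported times are simply too long goes further than the SAP supports. Dating every patient at the end of the confirmation period would be coherent. The fault is that only one route does so.

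**A reader might infer that any marker that prolongs ICU stay will appear to delay liberation.** The definition does not have that effect. Every stay of two days or more after D gets the same date, so only the share discharged on D matters.

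**The marker link is indirect.** Background and Rationale says nothing about discharge timing, and for PECAM-1 it gives no link to organ failure. This stands.

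**The study is exploratory.** Sample size and Statistical Principles both say so, which lowers the stakes. But p < 0.05 is still applied, and the Objectives hope to prompt clinical trials.

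**Conclusion.** The dating inconsistency is certain: it follows from the wording, and nothing else in the SAP repairs it. Equal ventilation durations receive primary-outcome times two days apart.

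The size of any bias is much less certain, and confidence in it is low to moderate. It requires a relation between marker and same-day discharge, which the SAP does not document. The unadjusted hazard ratios of about 0.92-0.97 (20% vs 10%) and 0.82-0.91 (40% vs 10%) rest on assumed shares and should not be read as what the adjusted models will show. At 10% vs 5% the effect is barely visible. Material inflation of false positives appeared only at 30% vs 10% and above. The point deserves correction because the rule itself creates the error and a common date removes it, not because the results are known to be distorted.

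**What to change.** 1. Date liberation in both routes to D, the last day with invasive or non-invasive ventilation. Use the following two days, in or out of the ICU, only to confirm it.
2. Apply the same rule to patients discharged on D+1, who at present have no event date.
3. Restate the competing-death window so that it covers the same period after D in all patients. For example, a death before the confirmation period ends counts as the competing event.
4. Keep the current dating as a sensitivity analysis, and report the share discharged on D by marker group so that readers can judge how much the dating matters.

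The cost is a short rewrite of Outcome Definitions and of the derivation code, using ventilation and readmission data that the current definition already needs. Reported times become up to two days shorter, events are confirmed retrospectively, and the death window has to be reworded.

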### Eligibility

The inclusion criteria consisted of age > 18, acutely admitted to the ICU and a presumed stay > 24 h. The exclusion criteria were non-obtainable informed consent or active treatment deemed futile by the treating clinician.

Included patients had study blood samples drawn daily for the first 5 days of their ICU-stay or until death or discharge, whichever came first.

For the present study in the Metabolomics cohort, only patients that presented with acute respiratory failure are included. Acute respiratory failure is defined as patients receiving either Invasive (IV) or Non-Invasive Ventilation (NIV) on the first day of ICU-admission.

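### Stopping ventilation on the day of ICU discharge counts as liberation whatever the reason, so some patients whose active treatment was given up are coded like patients who recovered

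*SAP*

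**What the plan says.** The SAP's Outcome Definitions section gives two routes to the primary event.

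- **ICU route:** "Liberation from mechanical ventilation is defined to occur on the second of two consecutive ICU-days without the need for either IV or NIV".
- **Discharge route:** liberation is "also considered to occur on the day of ICU discharge if cessation of mechanical ventilation occurs on the same day as ICU-discharge", limited to events "in patients that are not readmitted to the ICU within two days".

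The same section limits both routes by mortality: "The competing risk of death is said to occur if patients died before or within 24 hours from liberation from mechanical ventilation".

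Futility appears only in the Eligibility section, as a reason not to enter the cohort: "The exclusion criteria were non-obtainable informed consent or active treatment deemed futile by the treating clinician". The Withdrawal section concerns leaving the study (inclusion in error, no consent), not stopping treatment. No section says how to code ventilation stopped after inclusion because active treatment was given up.

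**The concern.** The two routes apply different tests. The ICU route asks whether ventilation was still needed. The discharge route asks only whether it stopped. A patient taken off ventilation because treatment is being limited satisfies the second test without having recovered.

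The SAP's Objectives section treats time to liberation as a patient-important outcome, to be used for prognostication and to motivate trials aimed at the endotheliopathy. Counting some dying patients as liberated mixes two opposite events in the primary endpoint. If the mixing is related to the marker, it distorts the effect the study sets out to estimate. The SAP itself defines this outcome in detail, so the gap cannot be put down to material left to a protocol.

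**Working it through.** **Step 1: apply the rule to one hypothetical patient.** The patient receives NIV on days 1 to 4. On day 4 ventilation is stopped after a decision to give up active treatment, the patient moves to the ward that day, and dies there on day 8.

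| Condition in the SAP | Result |
|---|---|
| Ventilation stops on the day of ICU discharge | Met, day 4 |
| No ICU readmission within two days | Met; the patient stays on the ward |
| Death before or within 24 hours of liberation | Not met; death comes four days later |
| Futility exclusion | Applied at entry only |
| Coded event | Liberation on day 4 |

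The death counts in the secondary 30-day mortality outcome, but that does not recode the primary event.

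On the ICU route, "two consecutive ICU-days without the need for either IV or NIV" does not settle the matter for a withdrawn patient who stays two more days in the ICU. One abstractor may read it as still needing ventilation, another as not receiving it.

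**Step 2: direction and size.** The SAP states no event count, withdrawal rate or effect size, so there is no figure to reproduce and every input below is an assumption. Compare a high-marker with a low-marker group, and let:

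- HR_L = marker hazard ratio for true liberation;
- HR_W = marker hazard ratio for withdrawals that pass the two limits and are coded as liberation;
- w = hazard of such withdrawals relative to true liberation in the low-marker group.

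The coded event has relative hazard 1 + w in the low group and HR_L + w × HR_W in the high group, so

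coded HR = (HR_L + w × HR_W) / (1 + w).

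| HR_L | HR_W | w = 1% | w = 5% | w = 10% |
|---|---|---|---|---|
| 0.70 | 2 | 0.713 | 0.762 | 0.818 |
| 0.70 | 1 | 0.703 | 0.714 | 0.727 |
| 0.70 | 0.70 | 0.700 | 0.700 | 0.700 |
| 0.70 | 0.50 | 0.698 | 0.690 | 0.682 |
| 0.90 | 3 | 0.921 | 1.000 | 1.091 |

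Worked cell: (0.70 + 0.05 × 2) / 1.05 = 0.80 / 1.05 = 0.762.

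The coded HR rises when HR_W exceeds HR_L, is unchanged when they are equal, and falls when HR_W is lower. With a weak true effect it can reach or cross 1.

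A simulation with constant hazards, competing death and censoring at 30 days (HR_L 0.70, HR_W 2) gave 0.712, 0.769 and 0.821 at w = 1%, 5% and 10%. Without the false events it gave 0.700 to 0.707. False events were 1.7%, 8.1% and 14.9% of coded liberations.

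**Step 3: dependence on same-day discharge.** A second simulation used a continuous marker, with daily hazards of 0.13 (liberation), 0.012 (death on ventilation) and 0.015 to 0.03 (withdrawal), and log hazard ratios per SD of −0.3, +0.4 and +0.6. It assumed that 10% to 40% of withdrawn patients outlive the 24-hour rule.

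- If all of those survivors leave the ICU on the day ventilation stops, the liberation HR per SD moves from about 0.73–0.75 to 0.75–0.80. That is an attenuation of about 5% to 28% on the log scale.
- If 30% of them do, it moves from 0.728–0.730 to 0.731–0.749, an attenuation of about 0% to 9%.

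**The case against.** The strongest objections are these.

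1. **The rule is not unlimited.** A reader might infer that any cessation on the discharge route counts as success. It does not: readmission within two days and death within 24 hours both remove patients. Only withdrawn patients who leave that day, are not readmitted and survive beyond 24 hours are affected. This stands and narrows the point. It does not remove it, because these are the patients the two limits do not catch.

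2. **The direction is not fixed by the text.** A reader might infer that the marker effect is necessarily pulled towards no effect. The SAP's Background says sTM and Syndecan-1 rise with severity, which makes more withdrawals at high levels plausible. It also says both correlate poorly with hypoxaemia at admission and need for ventilation, and it gives no severity or mortality link for PECAM-1. Adjustment for age, septic shock, heart failure, COPD, PAF-ratio, kidney injury and bilirubin may absorb part of any link between marker and withdrawal. This stands.

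3. **The size may be small.** Step 3 shows how strongly it depends on same-day discharge. With a weaker marker effect on withdrawal (log hazard ratio +0.2, withdrawal hazard 0.015, 25% outliving the rule, all counted), the HR moved only from 0.735 to 0.745. None of the simulations included covariates. This stands.

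4. **The results are exploratory and 30-day mortality is modelled separately.** Exploratory status explains the absence of power and multiplicity control. It does not justify giving an unrecovered patient a liberation event, and the mortality model leaves the primary outcome as coded.

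**Conclusion.** The point holds in a limited form. As written, the discharge route gives a wrong primary event to a patient whose ventilation is stopped because treatment is given up, who is not readmitted within two days and who lives beyond 24 hours. This follows from the wording and needs no assumption about rates. The ICU route is ambiguous for the withdrawn patient who stays two days.

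Bias of the liberation hazard ratio towards 1 is likely for sTM and Syndecan-1 if withdrawals are commoner at high levels. The documents support no such statement for PECAM-1. The calculated shifts are illustrations under assumed rates: from almost nothing, through 0.70 becoming 0.71 to 0.82, to crossing 1 when the true effect is weak. The bias is nil or reversed if the marker effect on withdrawal equals or falls below that on liberation. The SAP supports neither a definite attenuation nor a definite percentage.

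**What to change.** In Outcome Definitions, add one rule for both routes: ventilation that stops with a recorded decision to withdraw it, not to resume it, or to give up active treatment is not liberation.

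- **Identification:** classify from the EMR, blind to marker values, among all patients who stopped ventilation and whatever their later survival. Reviewing only those who died within 30 days would make event status depend on subsequent survival and leave withdrawn survivors coded as liberated.
- **Primary coding:** treat these patients as having a non-liberation competing event at cessation in the cause-specific model.
- **Sensitivity analyses:** report (a) the current coding, in which cessation alone suffices, and (b) coding as not liberated until death or day 30. Option (b) is better as a sensitivity analysis because it keeps patients at risk when liberation may no longer be possible. Under the Step 3 hazards it gave 0.705–0.725, against 0.728–0.730 when follow-up for liberation ended at cessation, a shift away from 1.

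The cost is a short change to the SAP, a limited record review, slightly fewer liberation events and some judgement in reading the record. It assumes that treatment-limitation decisions can be found in the EMR. The means largely exist: the Variables section already has marker-blind EMR adjudication for other items, and deaths are followed for a year.
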